### 2.5. Data Collection

#### 2.5.1. Assessing Primary Intervention Outcomes

First we assessed children’s health literacy, measured by two continuous variables (hygiene literacy and handwashing literacy scores) via questionnaire (Tables S3 and S4). Second we assessed child growth, measured by continuous variables (z-scores for height-for-age [HAZ] and body mass index-for-age [BAZ]) and binary variables (prevalence of malnutrition [stunting, undernutrition, and overnutrition]), via anthropometry (Table 1). HAZ is a linear growth indicator that indicates if the child has the appropriate stature for his/her age, while BAZ is an indicator of growth that indicates if the child has the appropriate ratio of weight and height for his/her age, according to WHO guidelines [4,29,30,31,32]. We used the WHO AnthroPlus (for children 5–19 years old) software (version 3.2.2., WHO, Geneva, Switzerland) to obtain HAZ and BAZ for each child. Third we assessed handwashing prevalence via observation according to standard operating procedure (SOPs) (Figure S3).

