After obtaining data from the children, research assistants completed the school restroom inspection checklist, took photos of WaSH facilities, and interviewed school principals or representatives, inputting all data into the app. We obtained school administrative data, e.g., budget for maintenance and other operating expenses, from the DepEd. At the end of each workday, research assistants discussed their work with each other, shared lessons learned, and identified areas for improvement. Upon accessing an internet hotspot, we used the app to transmit anonymized data to a central database via cloud storage. Research assistants periodically checked uploaded data to verify the completeness of data upload and identify discrepant, missing, or duplicate data. When needed, appropriate remedial action was taken, e.g., re-training research assistants or clarifying instructions for children.

After completing baseline surveys, we assigned two schools to the control arm and 13 schools to the intervention arm (Figure 3). We purposefully assigned two schools to the control arm because one school had a school principal who directly asked us to participate in our previous observational study. The other school was integrated (offering all possible grade levels, from kindergarten to grade 12) and was the location where we had pilot-tested our survey instruments before the observational study. We randomly allocated schools in the intervention arm to one of four groups. One research assistant and the research supervisor conducted randomization in Microsoft^©^ Excel as follows: (1) In one column, we listed the names of the 13 schools in the intervention arm, with one row representing one school. (2) In another column, we listed the four intervention groups (A, B, C, and D), with one row representing one group. We previously determined how many schools would be allocated to each group (Table S1). (3) In a third column, we used Excel’s random number function and ranked the schools, assigning each school to either group A, B, C, or D (Table S1). Except for the research supervisor, all research assistants, study participants (children), school personnel, and parents were blinded to the assignment of schools to the intervention arm and subsequent random allocation to intervention groups A–D.

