#### 2.5.4. Follow-Up and Other Assessments

Eight months later, we conducted a follow-up assessment by implementing the same methodology (i.e., 4-part school-based survey) that we used at baseline (Figure S3) and measuring the same types of outcomes (e.g., children’s health literacy and nutrition status, handwashing prevalence, school restrooms’ WaSH adequacy, and schools’ WaSH policies). Nine months later (17 months after the first health education session), we conducted a household questionnaire for children (Table S5). Thus, we were able to assess risk factors at the individual-, school-, and home-levels (Table 2).

We expected the intervention to influence children’s knowledge, behavior, and health outcomes. We defined indicators of the intervention’s impact as changes in children’s primary and secondary outcomes. We measured the difference between outcomes from the eight-month follow-up and baseline. We compared differences between control and intervention arms. We collected samples for water quality testing from study schools and a separate sample of households (located in the school neighborhood) after post-intervention assessments, as previously reported [27].

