### 2.8. Statistical Analysis

Because our study contains multiple arms (1 control and 4 intervention arms), it is necessary to develop a strategy for conducting statistical analysis that takes into account the study’s 5 arms, parallel design, and unequal allocation ratio between control and intervention arms. We will use an adjustment method to control for type I error due to the study’s multiple-arm design. Because we simultaneously assessed multiple outcomes, we will need to adjust for a possible multiple comparisons effect. One possible adjustment method is the Benjamini–Hochberg procedure [42], which controls for the false discovery rate (10%). We used unequal allocation, making the intervention group larger than the control group, because we aimed to increase the precision of the intervention comparison. Also, we aimed to make the study more acceptable to study participants and researchers by decreasing the likelihood of being allocated to the control group and not receiving the intervention. Because we aim to know whether and how interventions differ, we will not use a single global test of significance, which would compare all groups simultaneously. Rather we will use a dose-response model to examine trends. We will conduct all analyses by using the originally assigned intervention status (i.e., intention to treat), comparing each intervention arm against the control arm.

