#### 2.8.2. Inferential Statistical Analyses

To address study aims 1 and 3 (Figure 2), we will compare the study arms, using two-sided tests for primary outcomes. For continuous variables, we will use the *t*-test to calculate the mean weight differences between the control and intervention arms. For binary variables, we will use Poisson regression to compare the control and intervention arms according to their relative risk (RR). We will use multiple logistic regression models to analyze exposure-response: g = (E[Ai]) = β0 + β1Bi + γCi, where Ai is the primary outcome of interest, g( )  is the appropriate link function (identity for height and weight, logistic for stunting and poor health literacy), Bi is the continuous exposure of interest, and Ci is the vector of confounders. We describe proposed models in Box S2 and will describe full models in a forthcoming paper [25].

To assess risk factors of health, health literacy, and handwashing outcomes, we will use multiple logistic regression models that account for school-level clustering, estimate precision with 95% confidence intervals (CI), and *p*-values, and produce adjusted odds ratios (aORs). Clustering by school takes into account potential intragroup correlation among children from the same school and enables us to adjust the SE of estimates. aORs control for possible confounders (e.g., children’s age and sex, parent’s educational background and employment status, presence of toilet and handwashing basin inside home, household food insecurity). We will use confounders to calculate an adjusted effect estimate to account for baseline differences between the control and intervention arms. We will use three multiple logistic regression models (Box S2): (1) model A for poor hygiene literacy only, poor handwashing literacy only, and both poor hygiene literacy and poor handwashing literacy; (2) model B for malnutrition, i.e., stunting only, undernutrition only, and overnutrition only; and (3) model C for poor health status only, extreme hunger only, and both poor health status and extreme hunger.

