WaSH-related knowledge, attitudes, and practices (KAP) questionnaire for children	Self-reported: Demographics Perceptions about and use of school WaSH facilities Hygiene behavior (e.g., handwashing) Health history Food security	1 time: February–March 2017
Health examination (form) for children	Observed: Height Weight Urine specific gravity	3 times: February–March 2017; different sample of students during June–July 2017 and February–March 2018
Interview (form) for school principal ^(1)^	Self-reported: Perceptions about school WaSH facilities and students’ hygiene WaSH-related policies	2 times: March–June 2017; November–December 2018
School restroom inspection checklist	Observed: Availability, quantity, and quality of school WaSH facilities	2 times: February–March 2017; September–December 2018
Interview (form) for parent/guardian	Self-reported: Demographics Food security Hygiene behavior (e.g., handwashing)	1 time: March–June 2017
Home restroom inspection checklist	Observed: Availability and quality of home WaSH facilities	1 time: March–June 2017
Health literacy questionnaire for children	Self-reported: Demographics Understanding of hygiene concepts and handwashing	2 times: June–July 2017 and February–March 2018
Handwashing observation form	Observed: Children’s handwashing behavior	2 times: October 2017; February–March 2018
Water quality testing form	Observed: Indicators of water quality	1 time: April 2018 ^(2)^
Household questionnaire for children	Self-reported: Demographics Perceptions about school and home WaSH facilities Hygiene behavior (e.g., handwashing) Health and nutrition status Food security Exposure to second-hand smoke Home and household characteristics Parent/guardian’s education and employment	1 time: November 2018–February 2019
N/A	Secondary school administration data ^(3)^	Various

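### For stunting, undernutrition and overnutrition, the stated between-arm Poisson relative risk does not estimate the pre-to-post effect the plan defines, and the plan does not say whether it or the mixed model governs

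*Protocol article*

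**What the plan says.** - **Outcomes.** Section 2.5.1 lists among the primary outcomes the "binary variables (prevalence of malnutrition [stunting, undernutrition, and overnutrition".
- **Effect.** Section 2.5.4, in line with the Abstract, defines impact as change compared between arms: "We measured the difference between outcomes from the eight-month follow-up and baseline. We compared differences between control and intervention arms".
- **Test.** Section 2.8.2 opens, for aims 1 and 3, with "we will compare the study arms, using two-sided tests for primary outcomes". For binary outcomes it then says: "For binary variables, we will use Poisson regression to compare the control and intervention arms according to their relative risk (RR". It names no baseline value of the outcome, no survey term and no arm-by-survey term.
- **Adjustment.** The next paragraph, on logistic models for risk factors, promises an adjusted estimate "to account for baseline differences between the control and intervention arms". Its example confounders are age, sex, and parental, home and food-security characteristics.
- **Mixed models.** The last paragraph of section 2.8.2 uses generalized linear mixed models (GLMMs), suitable for binary and continuous outcomes, to judge effectiveness. They estimate each intervention's effect against control and pre-to-post differences.
- **Control arm.** In section 2.5.3, "we assigned two schools to the control arm and 13 schools to the intervention arm". The two were picked deliberately: one principal had asked to join the previous observational study, and the other school had been the pilot site.
- **Data.** Table 2 records the children's health examination (height and weight) in the observational study and then in a "different sample of students during June–July 2017 and February–March 2018". The notes to Figure 2 and Table 2 say the trial children were revisited, so growth was measured at both trial surveys.

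**The concern.** A relative risk between arms compares levels. The effect in section 2.5.4 is a comparison of changes. Under randomisation to control the two would agree on average, and leaving out baseline would mainly cost precision. Here assignment to control was not random, so nothing balances baseline prevalence between two chosen schools and the other 13.

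Stunting and BMI-for-age category can be expected to move slowly, so prevalence at eight months will largely repeat prevalence at baseline. A level comparison would then report a pre-existing school difference as part of the intervention effect. The GLMM, read as an arm-by-time contrast, would not. With no order of precedence between them, the trial could report two different answers for one primary outcome, possibly in opposite directions.

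**Working it through.** **The plan's own figure.** The article gives no power, target effect or relative risk for this comparison. Its only sizing figure is N = 760. The Lynch formula with the stated population of 2,059,447, z = 1.96, and assumed p = 0.5 and d = 0.05 gives 384. Then 384 × 1.30 × 1.45 × 1.05 = 760.03, which reproduces it. That is a precision calculation for a prevalence and does not bear on this point.

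**Inputs.** Two control and 13 intervention schools (section 2.5.3); about 50 children per school (section 2.3), so about 100 against 650. Control prevalence is assumed to be 24.5%, the stunting figure for Philippine children aged 6–10 in section 1.1. The baseline gap, intraclass correlation (ICC) and tracking between surveys are not given and are varied as assumptions.

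**Step 1: what each quantity estimates.** Let b0, b1 be baseline prevalence in control and intervention, and f0, f1 follow-up prevalence.
- Level comparison: RR = f1/f0.
- Arm-by-survey contrast: (f1/f0)/(b1/b0).

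With no intervention effect and no change, f = b. The first then equals b1/b0 and the second equals 1. Pooling both surveys without an interaction also gives b1/b0, so the point does not depend on which survey the RR uses.

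**Step 2: a stable gap, no effect, control 24.5%.**

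| Intervention prevalence | Gap (points) | RR as stated | Ratio of RRs |
|---|---|---|---|
| 14.5% | -10 | 0.59 | 1.00 |
| 19.5% | -5 | 0.80 | 1.00 |
| 21.5% | -3 | 0.88 | 1.00 |
| 27.5% | +3 | 1.12 | 1.00 |
| 29.5% | +5 | 1.20 | 1.00 |
| 34.5% | +10 | 1.41 | 1.00 |

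For the -10 row, SE(log RR) = √(0.755/24.5 + 0.855/94.25) = 0.200. The 95% interval is exp(ln 0.592 ± 1.96 × 0.200) = 0.40 to 0.88, ignoring clustering. The -5 row gives 0.55 to 1.16 and the +10 row 0.98 to 2.02.

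**Step 3: conflict between the two analyses.** Take the -10 row and suppose prevalence in the intervention schools rises by a factor of 1.2 while control does not change. Follow-up is then 0.145 × 1.2 = 17.4%. The stated RR is 0.174/0.245 = 0.71, apparently protective. The contrast is 0.71/0.592 = 1.20, harmful.

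**Step 4: random school differences only, no effect.** Two simulations use different tracking assumptions.
- 50 children per school and 90% of stunted children still stunted: for ICC 0, 0.01, 0.03, 0.05 and 0.10, the central 95% range of the follow-up RR is 0.71–1.55, 0.66–1.71, 0.60–2.06, 0.55–2.40 and 0.47–3.62. The ratio of RRs stays within about 0.81–1.24 throughout.
- 47 children per school (703/15) and a latent growth score, ICC 0.05: the follow-up RR spans about 0.6–2.0. The ratio of RRs spans 0.73–1.37 at a between-survey correlation of 0.9, and 0.61–1.61 at 0.5.

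In the second simulation, the variance of the log ratio relative to that of the log RR is 0.29, 0.48 and 0.63 at ICC 0.05 for correlations 0.9, 0.7 and 0.5. At ICC 0.02 and correlation 0.5 it is 0.97 (0.91 in a second run), so the precision gain can be close to nil. Removal of a stable gap does not depend on that gain.

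**The case against.** A reader might infer that the plan ignores baseline for these outcomes altogether, or that any baseline gap will be reported as the intervention effect. The documents do not support that.
- The GLMM paragraph takes on the effectiveness question, covers binary outcomes, and names pre-to-post differences and comparison with control.
- The Poisson sentence gives only a model family and an effect measure. It does not say the RR is crude or confined to follow-up, and it could be read as carrying out the comparison of changes in section 2.5.4.
- The confounder list is only a set of examples, so it does not prove that the baseline outcome is left out.
- Section 2.8.2 refers to Box S2 and a forthcoming paper for model detail, and to Figure 2 for aims 1 and 3. None of these is shown.
- The Discussion admits the lack of randomisation to control, and section 2.8.1 plans pre- and post-intervention descriptions, so a gap would be visible.

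Most of this stands and limits the finding. It does not remove it. The Poisson RR is the analysis attached to two-sided tests of primary outcomes, and as stated it is a different quantity from the defined effect. The adjustment sentence sits with the risk-factor logistic models that produce odds ratios, not with the Poisson comparison. Box S2 is cited for the exposure-response and logistic models. Disclosing non-random assignment does not settle which estimate is the result.

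**Conclusion.** The point holds in limited form. Followed as written, the Poisson comparison does not estimate the between-arm difference in change, and it carries any stable baseline prevalence gap into the reported effect. The planned GLMM would remove such a gap, but the article does not say which analysis governs. It should be settled before results are reported.

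The size of the bias cannot be known from the article. Under no effect and 24.5% in control, gaps of -10 to +10 points correspond to RRs of 0.59 to 1.41 against a ratio of 1.00. The gap, ICC and tracking are assumptions, and the 24.5% describes ages 6–10, while the trial recruited grades 5, 6, 7 and 10. The absence of the term from the full plan is not proved. Only the article's own wording is at issue.

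**What to change.** In section 2.8.2, state that for stunting, undernutrition and overnutrition the effect estimate and two-sided test are the arm-by-survey contrast. Either route will do:
1. Fit the Poisson model to both surveys with arm, survey and arm-by-survey terms and allowance for school clustering. Report the interaction as a ratio of prevalence ratios.
2. Name the arm-by-time contrast of the planned GLMM as primary, and state its scale, since a logit link gives odds ratios.

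Label any follow-up RR descriptive and print it next to the baseline RR.

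The cost is a wording change and a little programming. No new data are needed, because height and weight were taken at both trial surveys. The contrast may be no more precise than the follow-up RR if school differences are small and the outcome tracks weakly. It also does not protect against differential trends between two non-randomised control schools and the other 13, so that limitation should stay in the interpretation.

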## 2. Research Methodology

### 2.1. Study Overview and Design

WaSH in Manila Schools was a research project aimed at improving children’s environmental health by addressing inadequate school WaSH and promoting health literacy and hygiene practices (Figure 2). We implemented the project from January 2017 to February 2019, first conducting an observational study [27] to assess the WaSH situation in 15 public schools in Metro Manila, and then conducting a longitudinal study to develop, implement, and evaluate WaSH interventions in the same public schools (Figure 2). We conducted a cluster-RCT to address three specific aims (Figure 2) and compare the efficacy of four school-based WaSH intervention packages. Each intervention package consisted of different combinations of four elements: (1) WaSH policy reinforcement, (2) health education, (3) hygiene supplies, and (4) WaSH facilities (e.g., toilets, urinals, handwashing basins) improvements (Table S1).

This was a two-arm cluster-RCT (Figure S1), with one intervention arm and one control arm. The control arm received no intervention, rather the “standard of care”, which we defined as WaSH policy reinforcement, a hygiene workshop for teachers, and two health education sessions. The intervention arm was further divided into four groups (A, B, C, and D), based on the volume (low, medium, or high) of health education provided. Cluster units were public schools located in three cities of Metro Manila, Philippines, where many people, including a majority of public school children, were exposed to inadequate WaSH.

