### 2.3. Sampling and Recruitment

We conducted formative research (Figure S2) to prepare for the implementation of our intervention. We previously described how we estimated the sample size using the Lynch formula [27]. The target population was all the public school children in Metro Manila, where in School Year 2014–2015 a total of 2,059,447 public school children (1,373,852 elementary and 685,595 secondary school children) were enrolled [23]. We inflated the sample by 30% and 45% to account for nonresponse and refusal, respectively, and then inflated the sample by another 5% to account for differences in schools’ enrollment sizes. The target sample size was N = 760; we enrolled 756 students at baseline and 703 students at the 8-month follow-up (retention rate: 86%) (Figure 3).

We selected schools located in Manila, Navotas, and Quezon City (Figure 4) because they were geographically and demographically representative of cities in Metro Manila. We recruited the school principals from the 15 public schools that participated in our previous observational study [27]. We used convenience, rather than probabilistic, sampling, choosing to revisit the same 15 schools because of existing relationships of trust and cooperation with school principals and personnel. These factors can facilitate communication and collaboration, which were crucial because we aimed to maintain a long-term working relationship with schools in spite of our limited resources in time, personnel, and materials. We previously described our multi-stage cluster sampling strategy [27]. Based on the school’s enrollment size, 1–2 class sections were selected to obtain a target sample of ~50 students per school. We recruited entire class sections as a whole rather than groups of students from multiple class sections so as not to interrupt on-going classroom instruction with our research activities. We decided not to re-recruit the students from our previous observational study as a new school year had begun, resulting in students advancing up to the next grade level (e.g., from grade 5 to 6) and moving to different class sections, as well as some students transferring to different schools that were not involved in our study. No monetary reimbursement was offered to school principals, and all schools were compensated (Table S6) with printed research portfolios, certificates of appreciation, classroom viewings of an educational film promoting handwashing, and hand hygiene gel.

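### The arm comparisons named for primary outcomes (t-test, Poisson) make no stated allowance for school clustering, and nothing says which analysis governs

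*Protocol article*

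**What the plan says.** Schools were the assigned units. Section 2.1: "Cluster units were public schools located in three cities of Metro Manila, Philippines". Section 2.5.3: "we assigned two schools to the control arm and 13 schools to the intervention arm". Section 2.3 adds that "1–2 class sections were selected to obtain a target sample of ~50 students per school", taken as whole class sections.

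For aims 1 and 3, section 2.8.2 announces two-sided tests for primary outcomes. Continuous variables get a t-test "to calculate the mean weight differences between the control and intervention arms". Binary variables get a Poisson model: "For binary variables, we will use Poisson regression to compare the control and intervention arms according to their relative risk (RR". Neither sentence mentions school, a clustered variance or a school-level analysis.

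The next paragraph of 2.8.2 covers the multiple logistic models for risk factors. There clustering is stated with its reason: "Clustering by school takes into account potential intragroup correlation among children from the same school and enables us to adjust the SE of estimates". That paragraph also promises a confounder-adjusted estimate to account for baseline differences between arms.

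The closing paragraph of 2.8.2 gives GLMMs the task of judging whether the intervention worked and of estimating each intervention's effect against control. No sentence says which of the three approaches decides a primary outcome.

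On size, section 2.3 says "We previously described how we estimated the sample size using the Lynch formula" and "The target sample size was N = 760; we enrolled 756 students at baseline and 703 students at the 8-month follow-up".

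**The concern.** Children in one school share teachers, toilets, neighbourhood and intervention, so their outcomes are correlated. A t-test on individual children treats roughly 700 children as independent when only 15 units were assigned, two of them controls. Its standard error is then too small and its p-values and intervals too optimistic.

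This is more than an article's brevity. The section explains clustering for one set of models and leaves it off the tests it names for the primary outcomes. Three approaches can give three answers to one question, and a reader cannot tell which p-value is the result.

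**Working it through.** **Inputs from the protocol article.** 2 control and 13 intervention schools. Children per school: 703/15 = 46.9 at follow-up, 756/15 = 50.4 at baseline, so m = 47 and m = 50 are used. Prevalence 24.5% is the stunting figure for ages 6–10 in section 1.1.

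**Assumptions.** ICC 0.01, 0.02, 0.05, 0.10 (none is given). Nominal two-sided 5% per test (no per-test level is given; section 2.8 mentions a 10% false discovery rate as one option). A second prevalence of 50%.

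**1. The plan's own figure.** The Lynch formula is n = N·Z²·p(1−p) / [N·d² + Z²·p(1−p)]. With N = 2,059,447 (section 2.3) and assumed Z = 1.96, p = 0.5, d = 0.05, n = 384.1. Applying the stated inflations for nonresponse, refusal and enrolment size: 384.1 × 1.30 × 1.45 × 1.05 = 760.2, against the stated 760. No factor is a design effect, and no difference between arms enters.

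**2. Unclustered t-test.** Design effect DE = 1 + (m−1)·ICC. True false-positive rate = 2·[1 − Φ(1.96/√DE)].

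| ICC | DE, m = 47 | rate, m = 47 | rate, m = 50 |
|---|---|---|---|
| 0.01 | 1.46 | 10.5% | 10.8% |
| 0.02 | 1.92 | 15.7% | 16.4% |
| 0.05 | 3.30 | 28.1% | 29.1% |
| 0.10 | 5.60 | 40.8% | 42.0% |

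Simulation of 2 vs 13 schools of 47 (20,000 runs) gave 10.5%, 15.7%, 28.1% and 40.7%.

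**3. Plain Poisson on a yes/no outcome.** The Poisson model variance exceeds the binomial one by the factor 1/(1−p), so DE is replaced by DE·(1−p). With m = 47:

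| ICC | p = 24.5% | p = 50% |
|---|---|---|
| 0.01 | 6.2% | 2.2% |
| 0.02 | 10.4% | 4.6% |
| 0.05 | 21.4% | 12.7% |
| 0.10 | 34.1% | 24.2% |

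The two errors cancel where DE·(1−p) = 1. At p = 50% that is DE = 2, or ICC = 1/46 = 0.022. Below it the test is conservative.

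**4. Would a cluster-robust standard error rescue the comparison?** With k equal-sized schools in an arm, the sandwich estimate of that arm's variance has expectation (k−1)/k² times the between-school-mean variance, where the true factor is 1/k. For 2 vs 13 schools, including the usual correction (15/14)·(704/703): (1/4 + 12/169) × 1.073 = 0.344, against a true 1/2 + 1/13 = 0.577. The variance averages about 60% of the truth, and its control part rests on one degree of freedom. In the same simulation the type I error was about 22% with a t reference on 14 df and about 25% with a normal reference, at every ICC. Smaller runs ranged from 21% to 26%.

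**5. School-level comparison.** A t-test on school means (13 df) kept 5.0–5.2% in the same runs. Its standard error in SD units is √{[ICC + (1−ICC)/47]·(1/2 + 1/13)}. The noncentrality for 80% power on 13 df is 3.03.

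| ICC | SE | detectable difference |
|---|---|---|
| 0.01 | 0.134 | 0.41 SD |
| 0.02 | 0.154 | 0.47 SD |
| 0.05 | 0.201 | 0.61 SD |
| 0.10 | 0.262 | 0.79 SD |

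**The case against.** The strongest reply is that the article never calls the t-test or Poisson model the primary analysis. It says they are used for primary outcomes, gives the effectiveness question to GLMMs, and offers clustered logistic models with an adjusted estimate. A reader might infer that the trial's headline results will show several times the nominal error rate. The text does not support that: the inflation applies only if the unclustered tests are used for inference.

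A reader might also infer that the GLMMs ignore school because no school effect is mentioned. That is not supported either. The article refers to Box S2 and a forthcoming paper for its models, neither is shown, and random-effect structure and degrees of freedom are commonly left to such documents.

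Nor does the t-test figure carry over to Poisson. As shown, plain Poisson can fall below nominal for a common outcome at a low ICC.

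The plan also analyses pre-to-post differences, so the relevant ICC is that of change, which could be smaller. The detectable differences use unadjusted school means and may be pessimistic once baseline is included.

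All of this narrows the size of the problem. It does not answer the two textual points: the named tests carry no clustering while neighbouring models do, and no analysis is said to govern.

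**Conclusion.** The concern holds in a limited form. Section 2.8.2 names unclustered tests for primary outcomes in a trial that assigned 15 schools, sets them beside clustered logistic models and GLMMs, and does not say which decides.

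If the t-test were used for inference, its error rate would be about double the nominal 5% at ICC 0.01 and three times or more from about 0.02. For plain Poisson the inflation depends on prevalence as well as ICC. All of these sizes rest on assumed ICCs and a 5% level. Carrying the article's clustered standard errors over to the arm comparison would still fail, because there are only two control schools.

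The sample size is a secondary note. The fit to 760 is close but depends on assumed Z, p and d, and the full calculation is in an earlier publication not shown. It should be read as a prevalence-survey size without a design effect, not as a power calculation. Enrolment is complete, so the remedy is disclosure.

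**What to change.** In section 2.8.2, replace the t-test and plain Poisson comparisons with one governing analysis per primary outcome that includes school. This can be a mixed model with a school random effect, the baseline value and small-sample degrees of freedom (Kenward–Roger or Satterthwaite). For binary outcomes it can instead be baseline-adjusted school-level summaries, compared with a t reference on about (schools − 2) df. Do not rely on sandwich standard errors for the arm comparison. Say that the other models are supportive, and report the ICC for each primary outcome.

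In section 2.3, add that 760 contains no design effect and is not a power calculation, and give the detectable difference over a range of ICCs as in step 5 of the working. Single-group comparisons with control involve fewer schools and will detect only larger differences.

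The cost is revised wording and re-run models, with no new data. Confidence intervals will be wider. The change does not remove bias from the purposeful choice of the two control schools, which the Discussion already acknowledges as a lack of randomization and which must stay as a stated limitation.
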